#### Calculation of sample size and statistical analysis

The sample size was calculated using the G * Power software (version 3.1.9.2) based on our previous pilot study (F test, repeated-measures ANOVA, intra-between interactions). Considering an effect size of 0.58 for the primary outcome (functional skills) and assuming a possible 10% dropout rate, a total of 30 patients (15 in each group) will be required to reach a 5% significance level with a 90% power. Descriptive statistics will be performed to determine the normality of the data and the mean change (standard deviation, 95% confidence interval) in each group will be calculated. GraphPad PRISM version 7.0 (GraphPad Software—San Diego, CA, USA) will be used for all analyses. A mixed factor ANOVA model will be employed to compare the effects of the interventions in each group in terms of functional variables (PEDI and EMG), quality of life questionnaire and social participation over time (pre-treatment, post-treatment and 30-day follow-up). A 95% confidence interval will be used to establish any differences and a p-value <0.05 will be indicative of a statistically significant difference between groups (two-tailed). If the supposition of normality is not met, pairwise comparisons between groups will be performed using a nonparametric test, as appropriate, for independent samples (Mann-Whitney U test) or dependent samples (Wilcoxon test). The alpha level will be adjusted to 0.0033 (Bonferroni correction) to avoid a type 1 error.

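### If normality fails, the plan replaces the group-by-time test with rank tests that are not defined as a between-arm comparison of change

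*Protocol article*

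**What the plan says.** All of this stands in the Protocol article, section on calculation of sample size and statistical analysis.

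- **Sizing.** The calculation is for "F test, repeated-measures ANOVA, intra-between interactions". It uses "Considering an effect size of 0.58 for the primary outcome (functional skills"), allows 10% dropout, and arrives at 30 children, 15 per arm, who "will be required to reach a 5% significance level with a 90% power".
- **Main analysis.** "A mixed factor ANOVA model will be employed to compare the effects of the interventions in each group". The outcomes are to be followed "over time (pre-treatment, post-treatment and 30-day follow-up").
- **Fallback.** Normality is to be judged from descriptive statistics, with no criterion given. The rule is then: "If the supposition of normality is not met, pairwise comparisons between groups will be performed using a nonparametric test". Two tests are offered, one of each kind: "for independent samples (Mann-Whitney U test) or dependent samples (Wilcoxon test").
- **Change.** Mean change with SD and 95% confidence interval is to be calculated in each group. No between-group test of change is named.
- **Significance.** "a p-value <0.05 will be indicative of a statistically significant difference between groups (two-tailed"). A Bonferroni-adjusted alpha of 0.0033 follows the fallback sentence.

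The Randomization section has two separately randomised arms. The Physiotherapy section gives both arms the same 12-week exercise programme.

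**The concern.** The trial asks whether children given active PBM change more than children given sham. The interaction test addresses that. The fallback does not say how it will.

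The sentence announces comparisons between groups, yet one of its two tests is for dependent samples. Children in different arms are not paired, so Wilcoxon can only compare visits within an arm. Both arms exercise and both may improve, so a within-arm result says nothing about PBM. The other test, Mann-Whitney, does compare arms, but on an unnamed variable. Applied to scores at a visit, it ignores baseline. Applied to change, it does not.

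The branch is also chosen from the trial data, with at most 15 children per arm and no stated rule. The primary score is a sum of 0/1 items, so the fallback may well be used. At stake are the power of the primary comparison in that branch and a clear statement of what it tests.

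**Working it through.** **1. The plan's own figure.** The interaction test uses λ = f²·N·m/(1−ρ), with m = 3 visits, df₁ = 2 and df₂ = 2(N−2). The protocol does not say whether 0.58 is f or d, and gives no ρ. Reading it as d (f = 0.29) with ρ = 0.5 and N = 27:

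λ = 0.0841 × 27 × 3 / 0.5 = 13.62; df = 2, 50; power = 0.904; 27/0.9 = 30.

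This reproduces the stated 30. Reading 0.58 as f gives N = 9, or about 12 after rounding to even and dropout, which does not match.

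**2. The effect used.** With an equal PBM effect d (in SDs of the score) at T1 and T2 and none at T0, f = d/√18, so f = 0.29 means d = 0.29 × 4.243 = 1.23. With 14 and 13 evaluable children, d = 1.22 gives 90% interaction power at ρ = 0.5. At other correlations d = 1.22·√[(1−ρ)/0.5] holds that power at 90%.

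**3. Power at two-sided 0.05, normal data, equal correlation between visits (simulated; error of about one point)**

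| ρ (assumed) | d | Interaction | Mann-Whitney, raw T1 | Mann-Whitney, change | Rank ANCOVA |
|---|---|---|---|---|---|
| 0.3 | 1.44 | 90% | 94% | 84% | 95% |
| 0.5 | 1.22 | 90% | 84% | 84% | 92% |
| 0.7 | 0.95 | 90% | 63% | 84% | 87% |
| 0.8 | 0.77 | 90% | 46% | 83% | 82% |
| 0.9 | 0.55 | 90% | 25% | 83% | 75% |

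*Hand check, raw scores.* Power ≈ Φ(d·√(0.955·n₁n₂/N) − 2.06), where 0.955 = 3/π is the efficiency of Mann-Whitney against the t test and 2.06 is the t critical value on 25 df. With n₁n₂/N = 182/27 = 6.741, the multiplier is 2.537. For ρ = 0.8: 0.77 × 2.537 − 2.06 = −0.11, power 46%. For ρ = 0.3: 1.44 × 2.537 − 2.06 = 1.59, power 94%.

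*Hand check, change.* The SD of change is √[2(1−ρ)], so the standardised effect is 1.22·√[(1−ρ)/0.5] / √[2(1−ρ)] = 1.22 at every ρ. The power is therefore flat, and it equals the raw-score figure at ρ = 0.5.

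**4. Skewed data, where the fallback would be used.** The same data were exponentiated (lognormal). Raw Mann-Whitney and rank ANCOVA use only ranks within a visit, so their power does not change. The untransformed ANOVA interaction falls to about 66%, 63%, 60%, 59% and 57% at ρ = 0.3, 0.5, 0.7, 0.8 and 0.9 with 14 active and 13 sham children, and to about 71% down to 59% with the arm sizes reversed. So raw Mann-Whitney beats the ANOVA up to ρ = 0.5, is close to it at 0.7, and loses at 0.8 and 0.9. Rank ANCOVA beats both at every ρ tried.

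**5. Within-arm Wilcoxon with no PBM effect.** The arms are independent, so the chance of a significant result in the active arm only is p_active × (1 − p_sham). With a true improvement of 0.8 SD of change in both arms, p is about 0.77 with 14 children and 0.73 with 13: 0.77 × 0.27 ≈ 0.21, about 20% in simulation. With 15 per arm, improvements of 0.3 to 0.8 SD of the score and ρ of 0.5 or 0.8, the simulated range is about 1% to 26%. With equal arms p(1−p) cannot exceed 25%, so the top figure includes simulation error.

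**The case against.** Three stronger readings are tempting, and the document supports none of them.

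*That the plan discards baseline.* It does not say so. Mann-Whitney on change fits the wording, and mean change is to be calculated in each group. The alpha of 0.0033 is about 0.05/15, and two arms by three visits give six cells and 15 pairs, which hints at raw cell comparisons. But the quality-of-life questionnaire also has 15 domains, so this settles nothing. What stands is that the variable is not named and no between-arm test of change is written down.

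*That the fallback costs half the power.* That needs ρ of about 0.8. At ρ = 0.5, the value that reproduces 30 children, the loss is about 6 points (90% to 84%). At 0.3 there is none. On skewed data the planned ANOVA loses power too, so comparing the fallback with 90% overstates its cost. The fairer comparator is a baseline-using rank test on the same data, and that test wins at every ρ tried, though by only about a point at 0.3.

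*That the plan will treat a within-arm result as proof of PBM.* It ties significance to a difference between groups and nowhere says otherwise. The Wilcoxon figures show the risk if results are read that way.

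It can also be said that an article leaves such detail to an analysis plan. That would excuse silence. Here the article fixes a rule, and the rule places a dependent-samples test under comparisons between groups.

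**Conclusion.** The point holds in this form. On a data-dependent check without a stated criterion, the plan moves from the interaction test it is sized on to tests that, as written, are not a between-arm comparison of change. It should be corrected. It concerns a contingent branch and does not invalidate the design.

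The size depends on two things the protocol does not state: the variable tested and the correlation between visits. With raw T1 scores, power against a 90% interaction test runs from 94% (ρ = 0.3) through 84% (0.5) to 46% (0.8) and 25% (0.9). With change scores it is 83–84% on normal data, and little is wrong beyond the wording. These figures assume 27 evaluable children, equal correlation between visits, an equal effect at T1 and T2, and alpha 0.05. Whether 0.0033 governs the fallback is a separate ambiguity and is not used here.

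**What to change.** Replace the fallback sentence with one pre-specified between-arm test that uses baseline:

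- Rank ANCOVA: regress the rank of T1 on arm and the rank of T0, and do the same for T2.
- If the analysis must stay with simple tests in PRISM, Mann-Whitney on change from T0 to T1 and from T0 to T2.
- State the normality criterion that triggers the fallback.
- Label within-arm Wilcoxon results descriptive and not evidence of a PBM effect.

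The cost is a few sentences and slightly more analysis work. Rank ANCOVA may need software other than PRISM, which the protocol names for all analyses, so that sentence may need a change too. Mann-Whitney on change has less power than raw scores if the correlation is below about 0.5 (84% against 94% at ρ = 0.3). Rank ANCOVA does not have that drawback. Neither option changes recruitment, visits or data collection.

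### Two significance levels, 0.05 and 0.0033, are set without saying which governs the primary outcome, and the sample size was calculated at 5% only

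*Protocol article*

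**What the plan says.** Everything is in one paragraph of the protocol article, under Calculation of sample size and statistical analysis. In order:

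- The calculation is for "F test, repeated-measures ANOVA, intra-between interactions", with this starting point: "Considering an effect size of 0.58 for the primary outcome (functional skills"). After a 10% dropout allowance, "a total of 30 patients (15 in each group) will be required to reach a 5% significance level with a 90% power".
- A mixed-factor ANOVA then covers PEDI, EMG, quality of life and participation "over time (pre-treatment, post-treatment and 30-day follow-up").
- The decision rule is a 95% confidence interval, and "a p-value <0.05 will be indicative of a statistically significant difference between groups (two-tailed").
- There is a fallback: "If the supposition of normality is not met, pairwise comparisons between groups will be performed using a nonparametric test", namely Mann-Whitney for independent samples or Wilcoxon for dependent samples.
- The closing sentence is "The alpha level will be adjusted to 0.0033 (Bonferroni correction) to avoid a type 1 error".

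The last sentence has no limiting words. It does not name the tests it covers, give the number of comparisons, or say whether the primary outcome is included.

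**The concern.** The paragraph fixes two different bars for significance and does not say which applies to functional skills, the primary outcome. A primary result with p between 0.0033 and 0.05 would be positive on one sentence and negative on another, and the choice could be made after the data are seen. A 95% confidence interval that excludes zero could also stand beside a verdict of no significance.

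The sample size rests on the 5% level alone. If the stricter level governs the primary test, the 90% power quoted for 30 children is no longer a supported statement about the trial.

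**Working it through.** **Inputs.** From the statistical section: effect size 0.58, alpha 0.05, power 90%, 2 groups, 3 visits, 30 children, 10% dropout (30 × 0.9 = 27 evaluable), second threshold 0.0033. Assumption: 0.58 is Cohen's f, the usual G*Power input for this test. Not given: the correlation ρ among visits, the nonsphericity correction ε, and the G*Power effect-size option.

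**1. Can N = 30 be reproduced?** For the interaction with 2 groups and m visits, df1 = (m−1)ε and df2 = (N−2)(m−1)ε. The noncentrality λ depends on the option:

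- default: λ = f²·N·m·ε/(1−ρ)
- as in SPSS: λ = f²·(N−2)(m−1)·ε

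N needed for 90% at 0.05 with m = 3 and f = 0.58:

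| Option | N | N/0.9, rounded up |
|---|---|---|
| default, ρ=0.5, ε=1 | 9 | 10 |
| default, ρ=0, ε=1 | 15 | 17 |
| SPSS, ε=1 | 23 | 26 |
| SPSS, ε=0.75 | 27 | 30 |

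The stated inputs do not fix N. One combination tried gives exactly 30, but the article does not say that it was used.

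**2. Power at 0.0033, taking the stated 90% as given (27 evaluable).** Solve for the λ that gives 90% at 0.05, then read the power at the stricter level.

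- 2-df interaction, df (2, 50): λ = 13.45. The critical F rises from 3.18 to 6.42, and power falls from 90% to 59%.
- 1-df contrast, df (1, 25): λ = 11.38. The critical F rises from 4.24 to 10.55, and power falls from 90% to 56%.

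So 90 − 59 = 31% to 90 − 56 = 34% of trials with that true effect would land between the two thresholds. Restoring 90% needs λ = 23.1 (ratio 1.72) or 21.4 (ratio 1.88), roughly that multiple of the sample.

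**3. Power at 0.0033, starting from f = 0.58 (27 evaluable, m = 3).**

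| Option | λ | Power at 0.05 | Power at 0.0033 |
|---|---|---|---|
| default, ρ=0.5, ε=1 | 54.5 | >99.9% | >99.9% |
| default, ρ=0, ε=1 | 27.2 | 99.7% | 95% |
| SPSS, ε=1 | 16.8 | 95% | 74% |
| SPSS, ε=0.75 | 12.6 | 90% | 58% |
| SPSS, ε=0.5 | 8.4 | 80% | 39% |

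**4. Where could 0.0033 come from?** 0.05/15 = 0.00333. Two groups by three visits give 6 cells and 6×5/2 = 15 pairs:

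- 3 compare the arms at the same visit;
- 6 compare visits within an arm;
- 6 compare one arm at one visit with the other arm at a different visit.

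The article also gives 15 domains for the Child Health Questionnaire, so the number alone does not identify the family.

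**5. The fallback branch.** Take 13 versus 14 children, normal data, and a standardised difference of 1.30, which gives a t-test 90% power at 0.05. Simulated Mann-Whitney power is about 88% at 0.05. At 0.0033 it is roughly 45 to 51%, depending on whether an approximate or exact p-value is used. This is an illustration with one between-group comparison, not the plan's own calculation.

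**The case against.** The strongest reply is that the order of the text limits the Bonferroni sentence. The ANOVA and p<0.05 come first; the nonparametric pairwise tests follow, and 0.0033 comes straight after them. Six cells give exactly 15 pairs, so an omnibus test at 0.05 with pairwise comparisons at 0.0033 is a coherent and common layout. On that reading the interaction keeps the level at which it was sized. This reading is plausible, but it is an inference from position and arithmetic. It also leaves a gap: when normality fails, no nonparametric interaction test is named, so the pairwise tests carry the primary question at the stricter level.

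A reader might infer that power simply drops to 59%, or that 90% can hold only at 5%. The documents support neither. They do not say that 0.0033 governs the powered test, and 59% is solved back from the stated 90% rather than derived from 0.58. Under two of the G*Power settings in the working, power at 0.0033 is still 95% or more.

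A reader might also wish to make a single post-treatment contrast the primary test. That goes beyond the defect, because the sample size was calculated for the group-by-time interaction.

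It is fair to say that listing a multiplicity family is often left to the analysis plan, and that the 6 cross-visit, cross-arm pairs make the correction conservative rather than inflating type 1 error. The point here is narrower: this article itself states two levels and does not assign them.

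**Conclusion.** The point holds in conditional form. The decision rule for the primary outcome is ambiguous for any p-value between 0.0033 and 0.05, and the sample size supports only the 5% level.

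- **If 0.0033 covers the primary test:** the 90% power is unsupported. It is about 59% (2 df) or 56% (1 df) if 90% at 0.05 is accepted with 27 evaluable children. From f = 0.58 it is anywhere from about 39% to over 99%, because the correlation, ε and effect-size option are not stated.
- **If 0.0033 covers only the nonparametric fallback:** the planned power of the interaction test is unchanged. However, a normality check in about 27 children then makes the bar for the primary question 15 times stricter, and power on that branch falls to roughly half in the illustration.

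Both readings need a correction to the text. Neither shows that the trial as planned has 59% power.

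**What to change.** 1. State that the primary test, the group-by-time interaction on PEDI functional skills as powered, is judged at two-sided 0.05.
2. State that the primary between-group comparison keeps that level if the nonparametric fallback is used.
3. Replace the unrestricted 0.0033 sentence with a Bonferroni or Holm correction limited to a listed family of secondary or pairwise comparisons. Leave out pairs that compare different arms at different visits.
4. If 0.0033 is kept for the primary outcome, recalculate and restate the power at that level, giving the correlation, ε and effect-size option.

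Items 1 to 3 change wording only and need no extra children; the price is that secondary outcomes carry weaker claims. Item 4 may show that more children are needed: about 1.7 to 1.9 times the sample if power at 0.05 is exactly 90%.

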#### Quality of life

Quality of life will be assessed using the Child Health Questionnaire—Parent Form 50, which is a useful tool that enables the assessment of a child’s quality of life from the parents’ perspective. This questionnaire has been translated, cross-culturally adapted and validated for the Brazilian Portuguese language [22] and was designed for children five years of age or older, addressing their physical, emotional and social wellbeing from the perspective of parents or caregivers. The questionnaire is composed of 50 items distributed among 15 domains. The final score of each scale ranges from 0 to 100, with higher scores denoting better function or sensation (better quality of life) [23].

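### The fixed Bonferroni threshold of 0.0033 is valid, but Holm's step-down holds the same 5% familywise error over the same comparisons and is never less powerful

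*Protocol article*

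**What the plan says.** The section on sample size and statistical analysis plans a mixed-factor ANOVA for PEDI and EMG, quality of life and participation over three time points. If normality fails, Mann-Whitney or Wilcoxon tests are to be used for pairwise comparisons. The paragraph then ends: "The alpha level will be adjusted to 0.0033 (Bonferroni correction) to avoid a type 1 error". It does not list the comparisons that share the corrected level.

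Three other statements bear on the point:

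- The same paragraph gives a second threshold: "a p-value <0.05 will be indicative of a statistically significant difference between groups (two-tailed").
- The sample size is computed at the uncorrected level. The children planned for "will be required to reach a 5% significance level with a 90% power".
- The Quality of life section describes the Child Health Questionnaire thus: "The questionnaire is composed of 50 items distributed among 15 domains". The analysis section does not connect that 15 with the 0.0033.

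**The concern.** Single-step Bonferroni holds each of the 15 comparisons in its family to 0.05/15, however many of the others have already been rejected. Holm relaxes the threshold after each rejection and still guarantees the same familywise error.

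The trial has 30 children, 15 per arm before dropout, so a comparison at 0.0033 has limited power unless the effect is very large. The Discussion expects improvement in functional performance, participation and quality of life together. If several outcomes in the corrected family do respond, fixed Bonferroni would leave undeclared some real differences that Holm would declare from the same p-values, with no extra recruitment.

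**Working it through.** **1. The plan's own figure.** 0.05/15 = 0.00333, which rounds to 0.0033. Neighbouring counts do not fit: 0.05/14 = 0.0036 and 0.05/16 = 0.0031. The family therefore has 15 members. Fifteen tests at 0.0033 give a familywise error of at most 15 × 0.0033 = 0.0495, or 1 − (1 − 0.0033)^15 = 0.0484 if independent. The correction is valid.

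**2. Which 15?** Two readings fit, and the article decides for neither:
- the 15 questionnaire domains;
- the pairwise contrasts among 2 groups × 3 time points = 6 cells, that is 6 × 5/2 = 15.

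**3. Holm against Bonferroni, for any 15.** Order the p-values p(1) ≤ … ≤ p(15). Holm compares p(i) with 0.05/(16 − i) and stops at the first failure. The thresholds are 0.0033, 0.0036, 0.0038, 0.0042, 0.0045, 0.0050, 0.0056, 0.0063, 0.0071, 0.0083, 0.0100, 0.0125, 0.0167, 0.0250, 0.0500.
- *Power.* No threshold is below 0.05/15. A p-value that passes Bonferroni, and every smaller one, passes Holm too, so Holm's rejections include Bonferroni's.
- *Error.* Suppose m0 hypotheses are truly null. At the first false rejection at least m0 hypotheses are still untested, so the threshold is at most 0.05/m0. The chance that any of the m0 null p-values falls that low is at most m0 × 0.05/m0 = 0.05, whatever the dependence.

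**4. Size of the gain.** This part rests on assumptions: 15 parallel two-sample t-tests, correlation 0.5 between scores, and the same standardised difference d on every affected score. The values of d are chosen as follows:
- 0.58 is the stated effect size read as d.
- 1.16 = 2 × 0.58 is the same figure read as Cohen's f.
- 0.8 lies between them.
- 1.23 (15 per arm) and 1.33 (13 per arm) each give about 90% power for one test at 5%. Thirteen is the smaller arm after 10% dropout, since 30 × 0.9 = 27.

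Average power per truly affected score, Bonferroni → Holm:

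| d (per arm) | 1 of 15 real | 5 of 15 | 10 of 15 | 15 of 15 |
|---|---|---|---|---|
| 0.58 (13) | – | gain 0.2–0.3 points | – | 5.6% → 6.6% |
| 0.58 (15) | – | gain 0.2–0.3 points | – | 7.2% → 8.7% |
| 0.8 (15) | 18.0% → 18.0% | 18.2% → 19.0% | 18.0% → 20.3% | 18.1% → 23.1% |
| 1.16 (15) | 50.3% → 50.3% | 50.0% → 52.2% | 50.1% → 56.2% | 50.0% → 63.5% |
| 1.23 (15) or 1.33 (13) | no difference | 56% → 59% | 56–57% → 62–63% | 57% → 71–72% |

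Dashes mark cases not tabulated. The chance of at least one true rejection is the same for both methods to within about 0.1 point, because both start at 0.0033.

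**5. Actual familywise error.** With 10 of 15 effects real at d = 1.23 to 1.33, it was 1.4–1.6% for Bonferroni and 2.9–3.1% for Holm. Both are under 5%.

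**The case against.** The strongest reply is that nothing here is wrong. Bonferroni is valid, familiar and conservative, and a sponsor may prefer it. That stands: the point is a better choice, not a mistake.

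Four further objections reduce its size.

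- **Scope.** A reader might infer that every comparison in the trial, including the primary PEDI test, is held at 0.0033. The text does not say so. The same paragraph uses 0.05 for differences between groups, and the 0.0033 sentence directly follows the nonparametric pairwise fallback. The point therefore covers only the corrected family, whatever it is.
- **Family.** If the 15 are pairwise contrasts of group by time, the simulation of 15 parallel scores does not describe them. All 15 could not then be real, because the baseline contrast between groups is null by randomisation. Holm's dominance still holds, but the table's largest gains do not carry over.
- **Size.** A reader might take the gain of 14 to 15 points as the expected loss. It needs very large effects on all 15 scores. The article claims 90% power only for the primary outcome, in a repeated-measures interaction, and gives no effect size for the other scores.
- **Error control and intervals.** A reader might infer that Bonferroni buys nothing. Its actual familywise error is lower when some effects are real, it bounds the expected number of false rejections, and it has simple matching simultaneous intervals. These properties are real. But the lower error is unused allowance under a 5% familywise target, the article sets no target for the number of false rejections, and it specifies only 95% intervals with no adjustment.

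**Conclusion.** The point holds as an optional improvement. That Holm rejects at least as much at the same 5% familywise level needs no assumption about effect sizes, dependence or which 15 comparisons are meant. The size of the benefit does: nil with one real effect, about 0 to 3 percentage points of average power with 5 of 15, and about 1 to 15 points with all 15, for d from 0.58 to about 1.3, correlation 0.5 and 13 to 15 children per arm. None of these inputs except the sample size and the bare figure 0.58 comes from the article.

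A reader might also infer that Holm would cure the mismatch between the 5% level behind the stated power and the 0.0033 threshold. It would not, because Holm's first step is also 0.0033. Which tests carry 0.0033, and whether the primary test stays at 0.05, is a separate question.

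**What to change.** In the section on sample size and statistical analysis, replace the fixed 0.0033 threshold with Holm's step-down at familywise 5% over the same corrected family. List that family's comparisons in the same sentence, and report Holm-adjusted p-values. Fix this before unblinding.

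The cost is about one sentence. No data collection changes, and the adjustment can be done by hand or in any package from the p-values already planned. In exchange, simultaneous intervals that match Holm are less simple to produce, and the actual familywise error sits nearer to 5% while remaining within it.
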